##### Actigraphy and biological measures

For 10 days during baseline, participants will be asked to wear the Dexcom G6 continuous glucose monitor to provide 24-h continuous glucose levels, the GENEActiv wristband (Activinsights Inc.) to collect activity and sleep data, and a wrist-worn iButton to collect distal temperature. Participants will perform at home salivary collection for DLMO and inflammation assessment. They will be asked to collect 6 buccal cheek swabs (every 3 h) across the course of one day to assess peripheral clock gene expression. Participants will be asked to visit Quest Diagnostics for a comprehensive metabolic panel (CMP) and glucose tolerance test.

#### Assessments after the baseline period

Participants will be asked to continue daily food logging throughout the 8-week intervention period. At 6 months after the end of baseline, participants will log their food (first intake and last intake) for 10 days in the app.

##### Mid-intervention

Participants will be asked to complete 8 days of sleep diaries (core CSD). Participants will wear the Dexcom G6 CGM to collect glucose levels continuously for 2 weeks and wear the GENEActiv (Activinsights Inc.) wristband to collect activity/sleep data for 3 weeks. Participants will perform at home salivary collection for DLMO assessment and collect buccal cheek swabs to assess peripheral clock gene expression. Participants will visit Quest Diagnostics for a CMP and glucose tolerance test.

##### Symptom, mood, and quality of life (QoL) assessments

Symptom severity and LIFE interview assessments will be conducted at the midpoint, at the end of the 8-week TRE period (week 10) and at 6 months after the end of baseline. Self-rated assessments of symptom severity and sleep/circadian variables will be conducted at each of those assessments and at 16 weeks post baseline. The EDE-QS will be administered at midpoint and post intervention. Participants will be asked to complete EMA for 7 days post intervention. Secondary outcome measures will be assessed post intervention.

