**Methods:**

One-hundred fifty participants diagnosed with BD 1 or II will be recruited via advertising in the local community. Main inclusion criteria include: obtaining medical treatment for BD; current sleep or circadian problems; self-reported eating period of ≥ 12 h; no eating disorder or other health conditions that would hinder or limit the safety of following TRE; and not currently experiencing a mood episode, acute suicidality, psychosis, alcohol or substance use disorder. Participants will be asked to complete a baseline period in which daily food intake is logged online for two weeks. After baseline, participants will be asked to follow TRE for 8 weeks and to continue to complete daily food logging during this time. Symptom severity interviews will be conducted by phone or videoconference at baseline, mid-intervention (6 weeks post-baseline), end of intervention (10 weeks post-baseline), and 6 months post-baseline. Self-rated symptom severity and quality of life data will be gathered online at the same time points as symptom severity interviews, and at 16 weeks post-baseline (6 weeks after the TRE period ends). To assess potential mechanisms of change, we will examine the change in diurnal amplitude of ‘clock’ gene expression as a primary mediator at 8 weeks compared to baseline. We will further test whether diurnal amplitude of clock gene expression is predictive above and beyond the role of two covariate potential mediators, glucose tolerance and inflammation at 8 weeks relative to baseline. To provide an index of whether TRE successfully decreases emotional lability, participants will be asked to complete 5 mood assessments per day for 7 days at baseline and at 10 weeks. These mood assessments will be optional.

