##### Secondary hypotheses

H4. TRE adherence will predict improvements in self-rated symptoms of mania and depression at 10 weeks and 6 months post-baseline compared to baseline symptom severity scores.H5. The degree of change in sleep and the amplitude of diurnal activity/distal temperature rhythms at week 8 will explain improvement in symptoms (week 10), controlling for baseline symptoms and sleep/diurnal rhythm amplitude.H6. The degree of change in metabolic health (CMP) at week 8 will explain improvement in symptoms (week 10), controlling for baseline symptoms and metabolic health.

To provide a more refined index of changes in emotion, we will assess the effects of TRE on daily emotional lability (as assessed using EMA, baseline and post-intervention).

We will conduct exploratory analyses to examine secondary outcomes (e.g., EMA) and potential moderators.

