### Trial design

The trial is a non-randomized, single arm (TRE) study. The primary endpoint is immediately after the 8-week-long TRE period (end of week 10). The follow-up assessments will be conducted at 6 months after the baseline, supplemented with post-baseline self-reported assessment at week 16. Hypothesized mechanisms of change will be tested at baseline and at 8 weeks post-baseline. The study setting is remote (online food plan materials, questionnaires, and interviews), supplemented with at-home collection of biological data (DLMO, clock genes, actigraphy, CGM) and assays completed by Quest Diagnostics (CMP, glucose tolerance test).

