#### Baseline assessment

Participants who meet the eligibility criteria will be asked to complete a two-week baseline. The baseline assessments will include daily food logs, sleep diaries, and EMA probes sent via smartphone app notifications, interview measures, self-report questionnaires, actigraphy, and biological measures.

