### TRE content

We will be careful to inform participants that our study does not involve dieting and that we expect them to sustain their caloric intake throughout the time following the TRE food plan. TRE will be administered as self-help via online instruction supplemented with optional coaching sessions and participant logging as previously described [69].

To minimize attrition and nonadherence, the food plan period is limited to 8 weeks. Participants are welcome to continue to access food plan materials and follow the food plan after the assigned 8 weeks. Individuals with personal and family experience with BD reviewed intervention content and their suggestions about the usefulness and modification of the material were incorporated [100, 101].

Because previous research has shown that interactive support improves adherence to web interventions [102], participants will be provided with opportunities to schedule 15-min online coaching sessions or to email questions about implementing TRE. We will encourage an initial coaching session. At one, three, five, and seven weeks into the TRE period, they will receive a link offering a chance to contact us or a link to a calendar to schedule a coaching appointment. Participants will be instructed that the scope of this coaching is narrow and will only focus on TRE. Participants will be invited to bring significant others, family members or household members to the coaching sessions if they’d like. Participants can send as many messages as they like using a contact form but will receive only one response per week. Coaching sessions will also be limited to no more than once a week.

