***Screening Self-Report***							
DIAMOND Self Report Screener Psychosis Subscale	SR	X					
Alcohol Use Disorders Identification Test (AUDIT)	SR	X					
Drug Use Disorders Identification Test (DUDIT)	SR	X					
Short Eating Disorder Examination Questionnaire (EDE-QS)	SR	X		X	X		
Insomnia Severity Index (ISI)	SR	X					
Munich ChronoType Questionnaire (MCTQ)	SR	X					
Brief Social Rhythms Scale (BSRS)	SR	X					

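### No scheduled eating-disorder measure after week 10, although benefit and eating times are followed to 6 months and participants may stay on the food plan

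*Protocol article*

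**What the plan says.** **EDE-QS schedule.** The section on symptom, mood and QoL assessments says "The EDE-QS will be administered at midpoint and post intervention". The EDE-QS row of Table 1 has marks at screening, mid-intervention and post-intervention (week 10), and none at week 16 or 6 months. Text and table agree, so this is a fixed schedule and not a detail left to a fuller document.

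**Exposure after week 10.** Under TRE content: "Participants are welcome to continue to access food plan materials and follow the food plan after the assigned 8 weeks".

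**Eating times after week 10.** At 6 months, "participants will log their food (first intake and last intake) for 10 days in the app".

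**Benefit after week 10.** In Table 1, MADRS, YMRS, LIFE and CGI are taken at 6 months, and QoL.BD, PHQ-9, PMQ-9 and PGI at both week 16 and 6 months. Secondary hypothesis H4 predicts "improvements in self-rated symptoms of mania and depression at 10 weeks and 6 months post-baseline".

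**Other harm monitoring.** The Risk management and Adverse events sections describe regular checks for relapse, new symptoms and adverse events, and refer to a cited source for the methods.

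**The concern.** The plan follows three things to 6 months: benefit, the timing of eating, and (by permission) continued use of the food plan. The one structured measure of eating pathology stops at week 10. Yet the article treats this risk as real. Eating disorder is an exclusion by history, by EDE-QS score and by diagnostic interview; coaches are asked to steer participants away from excessive restriction; and the scale is repeated during and at the end of the intervention.

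At stake is what the 6-month results can support. The trial could report sustained benefit at 6 months, including among people still keeping a restricted window, with no matching scheduled data on disordered eating. If such symptoms emerged in someone who kept restricting after week 10, no scheduled questionnaire or interview shown in the article is aimed at finding them.

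**Working it through.** The article states no figure on this point, so there is none to reproduce. The check has two parts: how long the gap is, and whether any other scheduled measure fills it.

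**1. Length of the gap**

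Inputs:
- Start of TRE, S. Baseline assessment: "Participants who meet the eligibility criteria will be asked to complete a two-week baseline". Hence S = week 2.
- End of TRE. Abstract: "After baseline, participants will be asked to follow TRE for 8 weeks". Hence 2 + 8 = week 10, which matches the primary endpoint in the Trial design section.
- Last EDE-QS, L = week 10 (text and Table 1).
- Last follow-up, F. Six months is taken as 26 weeks. The Trial design section counts it from baseline, giving F = 26. The two sections on assessments after baseline count it from the end of baseline, giving F = 2 + 26 = 28.

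The clock is supported by the Abstract, which places week 16 six weeks after TRE ends: 16 − 6 = 10.

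Share of time from TRE start to last follow-up that falls after the last EDE-QS = (F − L) / (F − S).

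| Reading | Weeks after last EDE-QS | Weeks from TRE start | Share |
|---|---|---|---|
| 6 months from start of baseline | 26 − 10 = 16 | 26 − 2 = 24 | 66.7% |
| 6 months from end of baseline | 28 − 10 = 18 | 28 − 2 = 26 | 69.2% |
| 6 months taken as 24 weeks | 24 − 10 = 14 | 24 − 2 = 22 | 63.6% |
| TRE counted from week 0, last EDE-QS at week 10 | 26 − 10 = 16 | 26 − 0 = 26 | 61.5% |

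The first two rows are the readings found in the text; the other two test sensitivity. Over all four the share is 62% to 69%. The article also places the mid-intervention assessment at 6 weeks in one place and week 8 in another. That should be reconciled, but it does not matter here because the last EDE-QS is at week 10 either way.

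**2. What else is scheduled after week 10**

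- Mood, QoL and global impression (week 16 and/or 6 months): these would show general worsening, but they are not measures of eating pathology.
- First and last intake at 6 months: this gives the eating window. It cannot show restraint or concern about eating, shape or weight, which the Measures section gives as the content of the EDE-QS.
- Open-ended questions on problems with TRE: these belong to the acceptability probes, marked in Table 1 at week 10 only.
- Coaching links: sent in TRE weeks 1, 3, 5 and 7. Barrier surveys: the last is at the end of week 9.
- Adverse-event and emergent-symptom checks: described, but their timing and content after week 10 are not shown.

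None of the scheduled items shown targets eating pathology after week 10.

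**3. After the fix**

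With the EDE-QS at week 16 and 6 months, the time with no later EDE-QS falls from 16 (or 18) weeks to 0. The intervals become 16 − 10 = 6 weeks, then 26 − 16 = 10 or 28 − 16 = 12 weeks.

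**The case against.** **Harm is still monitored.** A reader might infer from the schedule that harm is unobserved for two thirds of the time on or after TRE. The documents do not support that. Depression, mania, QoL and global impression are measured to 6 months and can show worsening. Routine checks for emergent symptoms and adverse events are described, and because their details sit in a source not shown, they cannot be assumed to stop at week 10 or to ignore eating. This stands, and it confines the point to the absence of a scheduled measure of eating-disorder symptoms.

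**The two thirds is not time on TRE.** A reader might also take the 67% as unmonitored TRE exposure. It is not. The assigned period has the EDE-QS during it and at its end. The later weeks are follow-up, in which participants are permitted, not asked, to continue, and the number who do so is unknown. This stands too.

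**The choice is coherent.** The aim is mechanistic, the primary endpoint is at week 10, people at higher risk are screened out, and participants are told that this is not a diet and to maintain their caloric intake. No stated hypothesis fails without the extra administrations. This is fair, and it limits the weight of the point. But H4 and the 6-month outcomes carry the trial's claims past week 10, and the sponsor already considers eating behaviour at 6 months worth recording. A benefit claim at that time is better supported with matching data on a harm the plan itself screens for.

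**Conclusion.** The point holds in a limited form. Text and Table 1 agree that the EDE-QS stops at week 10, and no other scheduled measure shown targets eating pathology from then to the 6-month follow-up. The gap is 16 weeks if 6 months runs from the start of baseline and 18 weeks if it runs from the end: 67% or 69% of the time from TRE start to last follow-up, and 62% to 69% over all readings tried.

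This rests on 6 months being about 26 weeks and on Table 1 being the full schedule of questionnaires and interviews. It does not show that harm in general goes unmonitored, nor how much TRE exposure falls in the gap. It is a worthwhile improvement in safety data and in what the 6-month results can support; it does not threaten the primary analysis.

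**What to change.** 1. Add the 12-item EDE-QS to the online self-report surveys already sent at week 16 and 6 months, and change the assessment text and the EDE-QS row of Table 1 to match.
2. Report EDE-QS change from screening beside the 6-month benefit results. Screening is the only value before TRE, and entrants were selected for scores below 15, so some upward drift from regression to the mean is to be expected and should be noted.
3. If results are broken down by whether the 6-month log shows a restricted window still being kept, label this descriptive. The groups are self-selected in a single-arm trial, and the comparison cannot attribute change to TRE.
4. Leave the handling of raised scores to whatever safety procedure the trial already applies. The article gives a score of 15 only as an entry criterion and describes no procedure for raised scores at midpoint or week 10, so none is proposed here.
5. State once whether 6 months runs from the start or the end of baseline.

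The cost is 12 items at each of two existing surveys, which is a small added burden for participants, and a protocol amendment.

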#### Training and reliability

Before commencing study interviews, interviewers will be trained to standardize administration and to attain high interrater reliability on all observer-rated measures (the DIAMOND, SCISD-R, C-SSRS, LIFE, MADRS and YMRS). Interrater reliability reviews will be conducted monthly on randomly selected recordings throughout the trial. If rater drift is identified, assessors will be retrained.

### Strategies to maximize data quality

As described elsewhere [69], we will use multiple criteria to assess potentially careless responses. These include strategies to detect and respond to inattentive responding, and data cleaning techniques.

### Risk management

As detailed elsewhere [69], risk management procedures are based on online intervention and psychoeducation websites for BD [98, 99]. These will include obtaining a release to contact a primary provider, careful training of all interviewers and coaches in how to assess and respond to high-risk symptoms and suicidality, routine assessments of possible relapse and emergent symptoms, and guidelines for providing sensitive referrals based on the urgency of the situation.

#### Adverse events

In addition to the risk management procedures, we will take several steps to minimize the potential for adverse events. For participants who experience the onset of symptoms, we will consider with participants whether it would be helpful to take a break from the study if requirements might interfere with placing a focus on recovery. For participants who choose to take a break from the study, and interviewers will schedule a time to check in to consider restarting trial engagement. Techniques for routinely assessing adverse events, responding to signs of adverse events, and reporting such events are detailed elsewhere [69].

#### Confidentiality

To protect confidentiality, we will hold to privacy standards that match or exceed those of all countries that we are recruiting in. For US participants, we have obtained an NIH Certificate of Confidentiality. All study personnel will be trained in confidentiality and privacy, through online CITI training as well as direct training provided by members of the executive team.

All participants will be assigned a study ID to be used in place of the participant’s name on all assessment materials. We will destroy the list linking IDs and names after study completion. Data for this project will be gathered using REDCap, a highly secure web-based research data collection system. REDCap provides several features to protect data security, including secure passwords required for staff log-in, well-defined levels of data access based on a staff member’s role in the project, data storage on servers located in ITG’s Advanced Computing Center which has locked physical security; use of an OHSU firewall and a second ACC firewall; and data transmissions that are encrypted with industry-standard SSL methods. Video contact with participants will be conducted by secure, HIPAA-protected zoom calls; participants have the option to turn off their camera during those meetings or to request telephone interviews in place of video calls.

### TRE content

We will be careful to inform participants that our study does not involve dieting and that we expect them to sustain their caloric intake throughout the time following the TRE food plan. TRE will be administered as self-help via online instruction supplemented with optional coaching sessions and participant logging as previously described [69].

To minimize attrition and nonadherence, the food plan period is limited to 8 weeks. Participants are welcome to continue to access food plan materials and follow the food plan after the assigned 8 weeks. Individuals with personal and family experience with BD reviewed intervention content and their suggestions about the usefulness and modification of the material were incorporated [100, 101].

Because previous research has shown that interactive support improves adherence to web interventions [102], participants will be provided with opportunities to schedule 15-min online coaching sessions or to email questions about implementing TRE. We will encourage an initial coaching session. At one, three, five, and seven weeks into the TRE period, they will receive a link offering a chance to contact us or a link to a calendar to schedule a coaching appointment. Participants will be instructed that the scope of this coaching is narrow and will only focus on TRE. Participants will be invited to bring significant others, family members or household members to the coaching sessions if they’d like. Participants can send as many messages as they like using a contact form but will receive only one response per week. Coaching sessions will also be limited to no more than once a week.

Coaches will receive guidelines and will meet with licensed clinical psychologists regularly throughout the intervention for support and to ensure that their coaching maintains fidelity to TRE and the dietary changes. Coaches will aim to provide a supportive, nonjudgmental environment where participants can discuss barriers and difficulties in implementing dietary plans and can receive behavioral tips. The focus of coaching will be on collaborative problem solving and empowerment in addressing barriers. Coaches will aim to help participants lessen self-criticism, to avoid overly ambitious or restrictive dietary changes, and to be sensitive to mood fluctuations that may make following this type of program difficult. Coaches will aim to help participants identify material in blogs, video clips, or other barriers materials that might help address the concerns raised.

Participants will have access to a website of information designed to address barriers to following their food plan (e.g., coordinating timing of food with family meals or holidays), improving sleep, or addressing light exposure. Barriers were identified by reviewing previous studies using TRE, by conducting a survey of individuals with BD who had tried TRE, and by reviewing concerns raised by those with lived experience of BD and/or following dietary programs. For each major barrier, brief tips are available, which vary in format (written, audio, or video); all tips are designed to take 2 min or less. To help participants access relevant materials, they will be sent a quick survey at the end of weeks 3, 5, 7, and 9 in the intervention period or post baseline asking if they had experienced any barriers and providing the option to view tips relevant to the barriers endorsed.

### Measures

The schedule of the assessments is provided in Fig. 1 and Table 1. Assessments will be performed as closely as possible to specified time points. Participants will be sent calendar links to sign up for their interview assessments. Self-report assessments will be completed online via a secure, encrypted online survey platform (REDCap). Probes for logs will be sent by text message for completion via cellphone or computer, and EMA probes will be sent via a smartphone app.

**Fig. 1 Fig1:**
[figure not shown]
Assessment timing

**Table 1 Tab1:** Schedule of assessments

Measure	Format	Screening	Baseline	Mid-Intervention (Week 8)	Post-Intervention (Week 10)	Week 16 Follow Up	6 Month Follow Up
***Screening Self-Report***							
DIAMOND Self Report Screener Psychosis Subscale	SR	X					
Alcohol Use Disorders Identification Test (AUDIT)	SR	X					
Drug Use Disorders Identification Test (DUDIT)	SR	X					
Short Eating Disorder Examination Questionnaire (EDE-QS)	SR	X		X	X		
Insomnia Severity Index (ISI)	SR	X					
Munich ChronoType Questionnaire (MCTQ)	SR	X					
Brief Social Rhythms Scale (BSRS)	SR	X					
